#### Primary outcome

The primary outcome is the difference in CMT in the treated eye, measured using spectral-domain OCT in both groups between selection and M2.

The micrometric CMT was converted into a logarithmic CMT (logSD-OCT) for statistical analysis, considering that the normal CMT was 250 μm.

The formula used in the trial is: logarithmic CMT = log10 (micrometric CMT/250).

Use of a logarithmic scale for analysing changes in CMT gives a more normal distribution for CMTs that coincides with the distribution of logarithmic visual acuity. Some studies have shown that the logarithmic transformation of the CMT provides a better picture of visual acuity [26, 27].

Our CMT results were expressed in microns and logSD-OCT so they could be compared with those in the literature.

A retrospective study in the department at CHU de Nantes on the effectiveness of triamcinolone injections in reducing CMT converted into logSD-OCT obtained the following results: between M0 and M1, −0.12logSD-OCT (*p* < 0.001) and between M0 and M3, −0.09logSD-OCT (*p* = 0.002), introducing the value of M2 as the main criterion.

#### Secondary outcomes

Secondary outcomes of the study are: 1) the scoring of “the moment” of injection on the day of injection (tolerable, uncomfortable, very unpleasant) and the rating on a visual analogue scale (from 0 cm = no pain to 10 cm = extreme pain); 2) visual acuity (ETDRS scale) at every visit to determine the gain between the inclusion visit and the follow-up visits (the mean scores for each arm will be compared at each follow-up visit); 3) the flare (using SL and LFM if available) at every visit to determine the reduction between the inclusion visit and the follow-up visit (the mean scores for each arm will be compared at each follow-up visit); 4) the vitreous haze at every visit to determine the reduction between the inclusion visit and the follow-up visit (the mean scores for each arm will be compared at each follow-up visit); 5) the thickness of the central macula of the treated eye to determine the duration of action at every visit (as stated in the objectives, the duration of action of the injection is determined by the reappearance of oedema; the mean scores for each arm will be compared at each follow-up visit); 6) AEs/SAEs including intermittent ocular hypertension, cataract, endophthalmitis, glycaemic and blood pressure imbalances at every visit; and 7) EQ-5D questionnaire on patient quality of life at every visit.

#### Efficiency outcomes

The incremental cost-effectiveness ratio (ICER; cost per quality-adjusted life-year (QALY)) will be calculated for the comparison between subconjunctival triamcinolone injection and intravitreal injection of a dexamethasone implant from a societal perspective and over a 6-month time period.

#### Measures used to determine the outcomes

OCT is used to accurately visualise the different layers of the retina, including the macula, using an infrared laser. This is a contactless examination which is noninvasive, painless and brief.

An LFM is a device used to measure the protein concentration in the anterior chamber using a helium–neon laser. This is a contactless examination that is non-invasive, painless and brief.

All the ophthalmic examinations performed at inclusion and during follow-up are common practice in ophthalmology. The visual acuity, IOP, examination using the SL and fundus examination form the basis of all clinical ophthalmic examinations. OCT is the test of choice for characterising and quantifying macular oedema, irrespective of type. This testing is contactless and is noninvasive, painless and brief. The values considered to be normal are: visual acuity, ETDRS 100; IOP, 12–21 mmHg; LFM, no proteinic flare or cellular Tyndall; fundus, no cellular Tyndall or vitreous haze; macula as described, normally LFM <10 ph/ms, CMT <300 μm and >250 μm.

The patient will be given the EQ-5D questionnaire validated in France [28, 29] at each visit to measure their quality of life. The EQ-5D consists of a questionnaire and a visual analogue scale. The questionnaire focuses on five areas: mobility, personal autonomy, current activities, pain/discomfort and anxiety/depression. There are three possible answers for each of these dimensions (EQ-5D-3 L), thus allowing for 243 health states. QALYs will be calculated for each arm using area under the curve methodology and the weighting coefficients available in France for the EQ-5D-3 L [29, 30].

#### Statistical methods

The data will be reviewed at the end of the study, prior to statistical analysis. The aim will be to review the progress of the study, identify potential problems and classify any minor or major deviations.

The variables measured at baseline will be described for all patients in both groups in terms of numbers and percentages for each category for categorical variables and minimum, maximum, average, standard deviation and quartile values for quantitative variables.

The primary endpoint is the difference in CMT in the treated eye between D0 and M2. CMT measurements will be converted into logarithmic CMT: logarithmic CMT = log10(CMT/250).

The main objective is to demonstrate the noninferiority of the group with subconjunctival triamcinolone injection compared with the group with intravitreal injection of a dexamethasone implant. The noninferiority margin was set at 0.06 (equivalent to CMT = 287). To demonstrate the noninferiority of the triamcinolone group versus the dexamethasone group, the 95% bilateral confidence interval (CI) of the difference between the two groups (dexamethasone – triamcinolone) will be estimated using a mixed linear regression model. This model will reflect the stratification factor of randomisation to the centre (the centre will be considered as a random effect) and will be adjusted according to the measurement at D0. The estimated upper boundary of the CI will be compared to the predefined noninferiority margin. If the upper boundary is less than 0.06, the noninferiority of the triamcinolone group as compared with the dexamethasone group will be demonstrated. For missing data, the worst observed value will be imputed for triamcinolone patients and the best value for dexamethasone patients. A sensitivity analysis will be performed with multiple imputation.

For secondary end points, the mean visual analogue scale score evaluating the moment of injection will be compared between groups using a linear mixed model; the score for the moment (tolerable, uncomfortable or very unpleasant) will be compared using the Mantel–Haenszel stratified Chi-squared test. A linear mixed model will be used to compare the change in ETDRS from D0 to 6 months between the groups. SL and LFM between D0 and 2 months will be compared between the groups using nonparametric Van Elteren tests (semiquantitative outcome). Duration of injection efficacy (duration is determined by the reappearance of oedema) will be compared between the groups using the Van Elteren test (semiquantitative outcome). Descriptions of AEs/SAEs will be reported in the two groups. Comparisons between the groups will be performed using Chi-squared or Fisher tests for intermittent ocular hypertension, cataract, endophthalmitis, glycaemic and blood pressure imbalances in both arms. There will be no imputation for missing data for these secondary end points.

For the economic assessment, mean costs and their corresponding 95% CIs will be presented. The ICERs will be estimated along with their corresponding acceptability curves, i.e. the curves indicating the probability that an intervention is cost effective conditional on society’s willingness to pay for an additional unit of effectiveness (i.e. an additional QALY gained) and considering the sampling uncertainty around the estimated ICERs.

As costs and ICERs are not normally distributed, the 95% CI and the cost-effectiveness acceptability curves will be determined using the nonparametric bootstrap resampling technique.

Sensitivity analyses will be performed for all end points, adjusted for the duration of macular oedema. All statistical tests will be bilateral. For secondary endpoints, a *P* value less than 0.05 will be considered statistically significant. Analyses will be performed using SAS statistical software (SAS Institute Inc., Cary, NC, USA).

As this is a noninferiority study, the analyses will be carried out on the intent-to-treat population and on the per-protocol population. The intent-to-treat population consists of all randomised patients in the study. The per-protocol population includes the most compliant patients, based on compliance with the inclusion and exclusion criteria, absence of major deviations from the protocol and availability of the main criterion.

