#### Sample size

This TRIOZ trial aims to demonstrate the noninferiority of subconjunctival triamcinolone injections compared to intravitreal dexamethasone implants. Noninferiority will be evaluated in terms of the difference in macular thickness in the treated eye between D0 and M2. The deadline of M2 was chosen based on the plan for the Huron study on dexamethasone (NCT000333814) and a retrospective study on triamcinolone at CHU Nantes. Preliminary data observed retrospectively in Nantes between 2011 and 2013 in 25 patients who received triamcinolone injections showed a decrease of 0.12 ± 0.12 log OCT at M1 (D0, 0.27 ± 0.11; M1, 0.15 ± 0.08) and of 0.09 at M3 (0.18 ± 0.11). The difference in macular thickness between D0 and M2 is assumed to be the same in the two groups and the common standard deviation is set at 0.12. The noninferiority margin was set at 0.06, the power at 80% and the type I error rate at 2.5%. Based on these assumptions, 128 patients are needed to demonstrate the noninferiority of triamcinolone compared to dexamethasone. A maximum rate of 10% for missing data is taken into consideration for M2 and 142 patients, or 71 patients per group, will therefore be randomised in the study.

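### The stated 80% power ignores the worst/best imputation rule that the primary intent-to-treat analysis applies to missing M2 values

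*Protocol article*

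**What the plan says.** Under Statistical methods, the outcome is the change in log10(CMT/250): "The primary endpoint is the difference in CMT in the treated eye between D0 and M2". The model has centre as a random effect and "will be adjusted according to the measurement at D0". The decision rule is: "If the upper boundary is less than 0.06, the noninferiority of the triamcinolone group as compared with the dexamethasone group will be demonstrated". The missing-data rule for this analysis follows directly: "For missing data, the worst observed value will be imputed for triamcinolone patients and the best value for dexamethasone patients". The next sentence is "A sensitivity analysis will be performed with multiple imputation".

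The same section defines the intent-to-treat population as everyone randomised, so imputed values enter it. The per-protocol population requires an available primary outcome, so they do not enter that one.

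Under Sample size, the change "is assumed to be the same in the two groups and the common standard deviation is set at 0.12". The other planning values are: "The noninferiority margin was set at 0.06, the power at 80% and the type I error rate at 2.5"%. This gives 128 patients. The allowance for missing data is: "A maximum rate of 10% for missing data is taken into consideration for M2 and 142 patients", that is 71 per group.

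**The concern.** Dividing 128 by 0.9 is the right allowance when a patient without an M2 value contributes nothing to the analysis. Under the stated rule such a patient contributes an extreme value, chosen against triamcinolone in both arms. That shifts the expected difference towards the margin even when the treatments are identical, and it widens the residual spread. The sample size section allows for neither effect.

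At stake is the main intent-to-treat result. A trial of two equally effective treatments could miss noninferiority because of a handful of absent measurements. The per-protocol analysis, which the rule does not touch, could succeed at the same time.

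**Working it through.** **Inputs from the article.** True difference 0, SD of change 0.12, margin 0.06, one-sided alpha 2.5%, 71 per arm, at most 10% missing (0.10 × 71 ≈ 7 per arm). Pilot SDs on the log scale: 0.11 at D0, 0.08 at M1, 0.11 at M3.

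**Assumptions of the check.** Normal data, missingness unrelated to outcome, equal numbers missing per arm, no centre effect simulated. Change is scored as reduction, so a positive dexamethasone minus triamcinolone difference is unfavourable to triamcinolone.

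**1. The plan's own figure.** n per arm = 2 × (1.96 + 0.842)² × (0.12/0.06)² = 62.8. With the t distribution this becomes 64, so 128 in total with 80.1% power. 128/0.9 = 142.2, hence 142. The figure reproduces.

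**2. Shift caused by the rule, group extremes, change imputed.** The expected maximum of 64 normal values is 2.34 SD.
- Extremes within arm: 2 × (7/71) × 2.34 × 0.12 = 0.055, about 92% of the margin.
- Extremes over both arms (128 values, 2.59 SD): 2 × (7/71) × 2.59 × 0.12 = 0.061.

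The residual SD rises from 0.12 to about 0.142. A rough power check within arm uses a standard error of 0.142 × √(2/71) = 0.0238. Then (0.06 − 0.0554)/0.0238 − 1.98 ≈ −1.78, which is just under 4%.

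**3. Simulated power on the planning assumptions** (change score, SD 0.12, 20,000 trials per row, extremes within arm).

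| Missing per arm | Mean shift | Power |
|---|---|---|
| 0 | 0 | 84% |
| 1 | 0.008 | 70% |
| 2 | 0.016 | 54% |
| 3 | 0.024 | 37% |
| 4 | 0.032 | 23% |
| 7 | 0.055 | 3.4% |

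With 7 missing and extremes over both arms, power is about 0.7%. If the number missing varies at random around 10%, power is 5.9% (within arm) or 2.6% (both arms).

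**4. Adjusted for D0, 7 missing per arm.** The D0–M2 correlation is chosen to keep the change SD at 0.12. For M2 SD 0.08 it is (0.11² + 0.08² − 0.12²)/(2 × 0.11 × 0.08) = 0.233. For M2 SD 0.11 it is 0.405.

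| Value imputed | M2 SD | Shift | Power within arm | Power over both arms |
|---|---|---|---|---|
| Change | 0.08 | 0.055–0.061 | 3.0% | 0.4% |
| Change | 0.11 | 0.055–0.061 | 3.3% | 0.7% |
| M2 value | 0.08 | 0.037–0.041 | 30% | 17% |
| M2 value | 0.11 | 0.051–0.056 | 6% | 1% |

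With nothing missing, the adjusted analysis has about 99.5% power at M2 SD 0.08 and 94% at 0.11. In the mildest group-extreme case (M2 imputed, SD 0.08, within arm), power is about 98%, 94%, 86% and 74% with 1, 2, 3 and 4 missing per arm.

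**5. The patient's own worst or best value.** The text does not exclude imputing each patient's own extreme from the visits that were made. Suppose D0 and M1 are available, with M2 mean 0.165, M2 SD 0.11 and M1–M2 correlation 0.6 (none of these is given in the article). With 7 missing per arm the shift is then about 0.014, and power is about 64% on the change score and 78% adjusted for D0.

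**The case against.** The strongest reply is that the rule is a deliberate safeguard. It works against the noninferiority claim, so a positive result under it would be hard to dispute, and the risk falls on the sponsor. Multiple imputation and a per-protocol analysis are prespecified beside it. This stands: the rule does not inflate type I error, and choosing it is legitimate. What does not follow is quoting 80% power alongside it without counting its cost.

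Three further points limit the size of the problem.
- Ten per cent is given as a maximum, and M2 comes only two months after an injection given in hospital. A reader might infer that the trial is bound to fail, or that its power is simply 3%. The article does not support that: 3% belongs to the ceiling, to group extremes and to the planning SD taken without D0 adjustment or with the change imputed.
- The model adjusts for D0. If the M2 value is imputed and its SD is as small as 0.08, power stays above 80% with three missing per arm.
- If each patient's own worst or best value is meant, most of the loss disappears.

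A reader might also conclude that the plan must require noninferiority in both populations. The article already provides both analyses; how they combine is a separate matter that an analysis plan may settle.

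**Conclusion.** The point holds as a mismatch between two stated parts of the plan. The sample size treats missing patients as lost, while the primary intent-to-treat analysis gives them extreme values. The 80% figure is therefore unsupported once more than a few M2 values are missing. On the planning assumptions one missing per arm is already enough to bring power below it; under the mildest group-extreme reading it takes four.

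No group-extreme reading examined exceeds about 30% power at the ceiling. That conclusion rests on equal true effects and on the simulation assumptions listed above. The per-protocol and multiple-imputation analyses are unaffected. A claim that the rule biases the trial towards a false positive would be wrong, because it acts in the opposite direction.

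**What to change.** Make the multiple imputation already planned the primary intent-to-treat analysis, drawing on the monthly CMT measurements already collected. Keep worst/best imputation as the extreme end of a tipping-point sensitivity analysis. This matches the logic of the 128-to-142 calculation. It costs protocol and analysis-plan wording only, with no new data. The small downside is less built-in protection against informative dropout, which the tipping-point analysis then has to show.

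If the sponsor keeps the rule as primary, restate the power under it for missing rates up to 10%, as a range. State whether the worst and best values are the group's (within arm or over both arms) or the patient's own, and whether the M2 value or the change is imputed. Either change should be made before the data are analysed.

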#### Follow-up visits

The monthly follow-up visits (M1–M6) allow for early detection of efficacy and complications (including ocular hypertonia) beginning within approximately 1 month [12, 23]. In addition, they provide reassurance for the patient and reduce protocol deviations and patients lost to follow-up.

The investigating physician will record any AEs/SAEs and any concomitant medications.

They will include the following in their examinations of the patient during visits M1, M2, M3, M4, M5 and M6 (visits M1 and M4 do not form part of the usual care): 1) measurement of CMT (by OCT); 2) measurement of visual acuity (using the ETDRS scale); 3) measurement of IOP; 4) examination of the anterior segment (by SL) for flare and crystalline lens clarity; 5) examination of the posterior segment (fundus) and nonmydriatic fundus photography for posterior vitreous haze; and 6) automated measurement of the flare (by LFM), if available. In addition, the patient will complete the EQ-5D questionnaire.

At M3 and M6, the patient’s blood pressure will be taken. A fluorescein angiograph is conducted at M2 and M6 if anomalies were detected at the inclusion visit. In addition, a blood sample will be taken at M6 to evaluate haemoglycaemia and fasting plasma glucose.

In cases of inadequate response or relapse between the M3 visit and the M6 visit, the investigator will be free to choose the appropriate treatment on the day that the inadequate response/relapse is detected, or later (± 30 days), at their discretion; follow-up visits will continue according to the initial schedule, i.e. monthly visits.

The research may be discontinued as a result of: 1) the patient withdrawing their consent; 2) necessity as decided by the investigator in case of SAEs that prevent the patient from continuing with the protocol; or 3) a decision by the authorities or the suspension/withdrawal of the drugs from the market.

In case of premature discontinuation from the study, the patient will be referred immediately to the investigator for a consultation to provide care for their disease. The premature end of study visit will be completed during this consultation.

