### Objectives and statistics

#### Objectives

The main objective of our study is to evaluate the efficacy of subconjunctival injection of triamcinolone in reducing CMT measured by OCT, the most objective, relevant and noninvasive criterion, compared with intravitreal injection of a dexamethasone 700 μg implant which has been approved for this indication, between the inclusion visit and 2 months after treatment (M2 visit).

The timeframe was chosen based on data from the Huron study of Ozurdex® [17, 24, 25] and data from our retrospective study on triamcinolone in the department at CHU Nantes [22].

The secondary objectives are: 1) evaluation of the experience of the injection; 2) evaluation of the effectiveness of the injection studied at each visit, measured by the gain in visual acuity (by the EDTRS scale; a key parameter of visual function), the reduction in flare and vitreous haze which are quantifiable ocular inflammatory parameters measured using an SL and LFM in centres equipped with this technology, the CMT measured using OCT (enabling evaluation of the duration of action of a subconjunctival triamcinolone injection compared with an intravitreal injection of a dexamethasone 700 μg implant; the duration of action of the injection is determined by the reappearance of oedema), the local and general tolerance of the two methods (collecting details of all AEs/SAEs) and the patients’ quality of life; and 3) economic evaluation of the efficiency (cost–utility analysis) of the subconjunctival triamcinolone injection compared with intravitreal injection of a dexamethasone implant from a societal perspective and over a 6-month period.

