### Adverse event management

There are no pharmacokinetic data in the literature for triamcinolone administered subconjunctivally. The clinical experience of the various centres performing these injections shows a duration of action of approximately 3 to 4 months for 0.3 and 0.4 ml, respectively. The duration of action of an intravitreal injection of a dexamethasone 700 μg implant is approximately 3 to 6 months.

Inflammatory macular oedema, a chronic and recurrent pathology, requires regular ophthalmological monitoring at least every 6 months, regardless of the type of treatment administered.

The most frequently occurring adverse reactions identified based on the summary of product characteristics for Ozurdex® and the experience of the University Hospital of Nantes for triamcinolone are: 1) corticosteroid-induced hypertension (eye tone will be monitored monthly until the effectiveness of any injected corticosteroid has been exhausted and at longer intervals thereafter based on blood pressure control); and 2) cataract (the visual acuity and appearance of the lens will be monitored using an SL during the usual follow-up consultations for inflammatory macular oedema until cataract surgery is performed).

All the AEs encountered that are observed by the investigator or reported by the subject during the study, whether or not they are expected (see the summary of product characteristics for Ozurdex®), should be documented in the AE section of the CRF.

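### The acuity model runs to 6 months with no stated D0 adjustment, and its contrast after M3 mixes the randomised injection with later free-choice treatment; M2 should be named as the comparison of the injections

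*Protocol article*

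**What the plan says.** All references are to the Protocol article.

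- **Objectives.** A secondary objective is "evaluation of the effectiveness of the injection studied at each visit, measured by the gain in visual acuity". The target is the injection, visit by visit.
- **Secondary outcomes.** The endpoint is "visual acuity (ETDRS scale) at every visit to determine the gain between the inclusion visit and the follow-up visits", with arm means compared at each follow-up visit.
- **Statistical methods.** The analysis named for acuity is: "A linear mixed model will be used to compare the change in ETDRS from D0 to 6 months between the groups". No covariates are listed. The primary CMT model, in the same section, has centre as a random effect and is adjusted for the D0 value. Secondary endpoints get no imputation. The one sensitivity covariate named for all endpoints is the duration of the oedema.
- **Follow-up visits.** "In cases of inadequate response or relapse between the M3 visit and the M6 visit, the investigator will be free to choose the appropriate treatment". Such treatment may be given at detection or up to 30 days either side, and "follow-up visits will continue according to the initial schedule, i.e. monthly visits".
- **Adverse event management.** For triamcinolone, centre experience "shows a duration of action of approximately 3 to 4 months for 0.3 and 0.4 ml, respectively" (the trial volume is 0.4 ml). For the comparator: "The duration of action of an intravitreal injection of a dexamethasone 700 μg implant is approximately 3 to 6 months".

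The article does not say how acuity values measured after retreatment enter the model.

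**The concern.** The objective concerns the effect of the injection that was randomised, but the named analysis extends over a period in which some eyes will have had something else as well. An eye that relapses at M4 and is treated contributes M5 and M6 letters that owe something to the second treatment. If the arm that relapses more is also retreated more, and retreatment works, the M6 difference shrinks.

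This matters for interpretation. Acuity is the main functional outcome, it is tested two-sided with no stated margin, and the trial is meant to support a cheaper injection. A null M6 result could be taken as showing that the two injections give the same vision.

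The second issue is precision. D0 acuity is measured in every patient, and the primary model uses its own D0 value. The acuity model is not said to do so.

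**Working it through.** **1. The plan's own figure.** The only sample-size figure concerns CMT at M2. With margin 0.06, SD 0.12, true difference 0, one-sided 2.5% and power 80%, the normal approximation gives 2 × (1.960 + 0.842)² × (0.12/0.06)² = 62.8, so 63 per arm or 126. The noncentral t gives 64 per arm (power 80.1%; 63 per arm gives 79.5%), which is the stated 128. Then 128/0.90 = 142.2, stated as 142. The figure reproduces. It concerns a visit before the retreatment window and says nothing about acuity.

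**2. Timing.** M1 and M2 precede the window, which opens at M3. Expected effect ends at about 3 to 4 months in one arm and 3 to 6 months in the other. Retreatment before M6 is therefore foreseeable on the document's own figures, and possibly at different rates in the two arms. M4, M5 and M6 are the exposed visits.

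**3. Do the other planned analyses deal with it?** Retreatment is permitted, so it is not evidently a major deviation that would remove a patient from the per-protocol set. The no-imputation rule concerns missing values, not values observed after retreatment. Adjustment for oedema duration does not address it. For slit-lamp and laser flare the article stops the comparison at 2 months; for acuity it does not.

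**4. Possible dilution (all inputs assumed; the document gives no retreatment rate and no ETDRS SD).** If a share f of each arm is retreated and retreated eyes end equal in both arms, the contrast retained is 1 − f. Power is shown for a true difference of 0.5 SD with 64 per arm (normal approximation):

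| f | Contrast retained | Power |
|---|---|---|
| 0% | 100% | 81% |
| 10% | 90% | 72% |
| 20% | 80% | 62% |
| 30% | 70% | 51% |
| 50% | 50% | 29% |

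For unequal relapse, suppose 50% against 30% of eyes relapse and each relapse costs 10 letters. The difference without retreatment is (0.50 − 0.30) × 10 = 2 letters. If retreatment restores a share q of the loss, 2 × (1 − q) letters remain: 2 at q = 0, 1 at q = 0.5, 0 at q = 1. These figures show the mechanism and are not estimates.

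**5. Baseline adjustment (correlation r assumed; equal SDs at D0 and follow-up).** The change-score variance is 2σ²(1 − r) and the residual variance after adjustment is σ²(1 − r²). The ratio is (1 − r²)/(2 − 2r) = (1 + r)/2.

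- r = 0.4: 0.84/1.20 = 0.70, so 30% lower variance.
- r = 0.7: 0.51/0.60 = 0.85, so 15% lower variance.
- Over r = 0.3 to 0.9 the ratio runs from 0.65 to 0.95, so the SE from raw change is 24% to 3% larger.

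This is a matter of precision, not bias.

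**The case against.** - **The article does not call the model unadjusted.** True. It lists no covariates, and covariates of secondary models are often left to the analysis plan, which is not shown. A reader might infer that baseline information is being thrown away; the text does not establish that. A repeated-measures model with D0 as a covariate or in the response vector would use it. What stands is that adjustment is stated for the primary model and not for this one.
- **The M6 contrast is legitimate.** It is. Retreated patients stay on schedule and the intent-to-treat set is analysed, so M6 compares two starting strategies as later managed. That also fits the 6-month cost-utility horizon. A reader might infer that M6 measures only the retreatment drug; that would need nearly every eye to be retreated, and nothing in the document says so.
- **Earlier comparisons are already planned.** Secondary outcomes does promise a comparison at each visit, which includes M1 and M2. Statistical methods, however, names only change to 6 months, and none of the visit contrasts is singled out as the comparison of the injections.
- **Unequal relapse would show elsewhere.** Duration of efficacy has its own between-arm test. That would reveal earlier relapse, but would not tell the reader how to interpret the acuity contrast.
- **Treatment choice is not unlimited.** Treatment visit bars later acetazolamide and systemic treatment at unstable doses. Crossing to the other arm's product is a fair inference, but is not stated.

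**Conclusion.** The point holds in a limited form. The acuity contrast at M4 to M6 estimates the effect of the starting injection plus later treatment, while the stated objective is the injection itself, and the article does not say which is meant. The contrast is valid as a treatment-policy comparison and is probably pulled towards zero. That direction rests on retreatment being effective and bringing the arms closer together. Its size cannot be computed, because the document gives no retreatment rate, ETDRS SD or correlation; the 10% to 50% loss of contrast shown above follows from assumed retreatment shares.

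The gain from D0 adjustment, 15% to 30% of variance at r = 0.7 to 0.4, applies only if the model would otherwise use raw change. Both matters concern a secondary endpoint. They are worth settling because the remedies are cheap and acuity is what readers will look at after CMT.

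**What to change.** 1. State D0 ETDRS as a covariate in the acuity mixed model, as the primary model does for CMT.
2. Fit the model over the monthly visits and name the M2 contrast, before the retreatment window, as the acuity comparison of the two injections. This brings Statistical methods into line with Objectives and Secondary outcomes.
3. Keep the M6 contrast, labelled as initial strategy plus retreatment. Report the number retreated by arm, and add a supplementary mixed-model analysis that sets aside acuity values after retreatment.

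**Cost.** Wording in the analysis plan and one extra analysis; no new visits or measurements. Monthly ETDRS and concomitant medications are already collected. The article does not say in so many words that the date of retreatment is recorded, so check that the case report form gives it.

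**Downside.** The supplementary analysis treats values after retreatment as missing at random. That is a strong assumption when retreatment is an open-label decision at the investigator's discretion, so the analysis should support the as-observed M6 result and not replace it.
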